**Figure 1 figure1:**
[figure not shown]
Study design of the randomized clinical intervention, the HAPPY trial, aiming to evaluate the use of an app-based program for healthy eating habits. HAPPY: Healthy eating using APP technologY; HbA_1c_: glycated hemoglobin.

### Ethical Approval, Trial Registration, and Consent to Participate

The trial was approved by the ethics committee of the Regional Ethical Review Board, Stockholm, Sweden (2018/652-31; 2018/1094-32; 2018/2393-32). The trial was registered at ClinicalTrials.gov (NCT03784612). All study participants receive oral and written information about the study and give their written informed consent prior to study start.

### Inclusion and Exclusion Criteria

Inclusion criteria are having type 2 diabetes diagnosed by a physician; being 18 years of age or older; having the ability to read and understand Swedish; having access to, and the ability to use, a smartphone; having a personal e-identification (ie, a secure, digital citizen e-identification solution to enable personal and secure identification in the app); and giving informed consent for participation. Both women and men are eligible for inclusion. No specific exclusion criteria apply.

### Intervention

#### Development and Content of the HAPPY Smartphone App

The primary aim of the intervention is to achieve an improvement in dietary intake and subsequent improvements in clinical variables and lifestyle factors through the use of a smartphone app for healthy eating habits among patients with type 2 diabetes. The content of the HAPPY smartphone app and the healthy eating behavior program is built into an existing digital platform developed by FRISQ AB. The program with its contents has been developed by researchers with experience in behavior change interventions (eg, physical activity), nutritionists, and active clinicians within primary and specialist care. It is based on a theoretical framework including the health belief model and the stages of change model, as well as on social cognitive theory [16]. Several techniques for behavior change, including general information, goal-setting strategies, self-monitoring, and feedback on performance, are included in the program [17]. The specific features of the HAPPY smartphone app are described below. The app is available both for iOS (version 11.4 and higher) and Android (version 5.0 and higher).

#### The HAPPY Smartphone App

Each week the user will be introduced to a new topic on healthy eating habits (eg, vegetable intake). The specific topics for each of the 12 weeks of the active intervention are outlined in Table 1. Following a short written introduction to the current topic, the user is given an activity to perform (eg, to add one portion of vegetables per day during that week or replace sugar-sweetened beverages with water during a week). Daily progress is recorded in the app, and automatic reminders (eg, notifications if the user has not responded to an activity) or feedback on the activity (eg, “Thank you for participating in the activity”) will be given. All study participants receive the same introduction and activity to perform. Reminders and feedback depend on the actions taken by the user.

**Table 1 table1:** Topics of the healthy eating program for each week of the intervention.

Week	Topic
1	Healthy food patterns
2	Vegetable intake
3	Regular eating habits
4	Sugar intake
5	More on vegetable intake
6	Slow and fast carbohydrates
7	Whole grains and fibers
8	Legumes
9	Saturated fat
10	Unsaturated fat
11	Salt intake
12	Beverages

Each topic (ie, each week) comprises information, recipes, short fun facts, or advice (ie, edutainment and an activity related to the topic). Every Monday, information and an activity that is linked to the theme of the week are available in the app. Recipes to inspire healthy cooking and facts or advice on healthy eating habits are introduced during the week on Tuesday, Wednesday, Friday, and Saturday. Every Thursday, the user receives a reminder of the activity, and at the end of the week, an evaluation about the activity is sent to the user. Each action (ie, reading the information text, recipes, short facts, or advice, and then performing the activity) is marked as read or completed in the app by the user. The status of an action in the app (ie, read vs not read or completed vs not completed) is also visible to study personnel. This information, together with information on each time a user has logged on to the app, is saved within the system. The structure of one week in the healthy eating program is presented in Table 2. Examples from the HAPPY smartphone app are shown in Figure 2.

**Table 2 table2:** Structure of weekly activities in the app.

Day	Content
Monday	Information and activity introduction
Tuesday	Recipe 1 and recipe 2
Wednesday	Short fact or advice 1
Thursday	Activity reminder: “How is it going?”
Friday	Recipe 3, recipe 4, and recipe 5
Saturday	Short fact or advice 2 and short fact or advice 3
Sunday	Activity evaluation: “How did it go?”

**Figure 2 figure2:**
[figure not shown]
Examples of screenshots from the HAPPY smartphone app. a) Each day, the specific activities for that day are displayed to the user. Before completing an activity, 0% of the activities for that specific day have been performed, as indicated by the large circle. By touching the screen where an activity is listed, the user is taken to a new page showing the activity in question. When an activity has been completed, this is indicated in the large circle as well as to the left of the activity in the list below the circle. b) At the bottom of the first page in the app, the user can choose the document symbol to display information (left-hand image), recipes (middle image), or short facts and advice (right-hand image). The user can access the documents at any time; for example, they can return to reread information or find favorite recipes. HAPPY: Healthy eating using APP technologY.

#### Download

At baseline, participants in the intervention group will download and be connected to the digital platform, where the study personnel (ie, trained nutritionists) can follow the individual progress of the user during the 12-week course on healthy eating habits in the app. Participants in the control group will be offered to download and be connected to the app at the 3-month follow-up. To avoid overlap with the 4-day food record, the app will be activated on the first Monday following the meeting with study personnel (ie, at baseline or the 3-month follow-up) and the intervention will thereafter follow for 12 consecutive weeks. An individual user account on the digital platform will be created for each participant by study personnel. Users will identify themselves in the app using a personal e-identification .

### Sample Size and Power Calculations

A total of 168 patients (84 per group) will provide 80% power at a 5% significance level to detect a clinically significant change of 4 mmol/mol in HbA_1c_ [18]. A standard deviation of 11.8 mmol/mol was estimated based on the average HbA_1c_ level (mean 53.4 mmol/mol, 95% CI 53.3-53.5) in Stockholm County in 2016 using data from the National Diabetes Register [19]. Based on earlier intervention studies within similar populations, a dropout rate of around 20% is expected. To cover for potential dropout, we will recruit a total of 200 patients (100 per group).

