## Methods

### Study Design

The HAPPY trial is a randomized clinical trial with two arms. The research team behind the design of the smartphone app and the study includes nutritionists, epidemiologists, statisticians, and clinicians. The intervention is described according to the CONSORT (Consolidated Standards of Reporting Trials) statement [14] and the CONSORT-EHEALTH (Electronic and Mobile HEalth Applications and onLine TeleHealth) checklist developed specifically for eHealth and mHealth interventions [15].

Patients with type 2 diabetes who volunteer to participate are recruited from primary health care centers in the center and suburbs of Stockholm. Data collection is performed in collaboration with clinicians and nurses at the centers, where they give a brief introduction of the study to their patients. Information about the study is also available in the waiting rooms of the centers, and patients can contact study personnel directly if they are interested in participating. The included primary care centers differ in size, and the number of eligible patients can vary. Those interested in participating in the study are contacted by phone by study personnel and are given more information. Patients that fulfill inclusion criteria and agree to participate are sent an email with a link to the baseline questionnaire, including a web-based consent form. They are thereafter scheduled for a meeting with study personnel. During this meeting, participants sign an additional written informed consent form in order to verify that they fully understand the web-based information. Thereafter, baseline measurements are performed and patients are then randomized 1:1 to the intervention or control group. All participants are followed up after 3, 6, and 12 months.

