Noteworthy strengths of the HAPPY trial include the randomized design, a large sample size, objective assessment of outcomes (eg, measured clinical and anthropometric variables), and a priori calculation of statistical power. Further, the content of the HAPPY smartphone app was developed in collaboration with researchers, clinicians from primary care, and specialists from endocrinology clinics. The digital platform allows the patient and care provider to work together. This increases the chance of effectiveness, as interventions including both the health care system and patient have been found to be more effective than those targeting only one or the other [40]. Nevertheless, a limitation to our study is the lack of a pilot study testing feasibility and acceptability of the app among users. However, the healthy eating program is built into an existing digital solution that has been rigorously tested and is continuously updated to allow for the rapid development of iOS and Android systems. The stability of the digital solution is a strength, as users are less likely to stop using the app due to technical malfunctions. The use of various behavioral change techniques from different theoretical domains may also increase user engagement and decrease attrition in our study. Within the HAPPY trial, we are also collecting data on user engagement with, and usability of, the app and the healthy eating program.

A 4-day food record is used to assess dietary intake at baseline and follow-up. Although most dietary assessment methods are subjective and susceptible to social desirability, a food record has the advantages of being prospective (ie, does not rely on memory) and open ended with no limitation on what items can be reported. In the event of potential missing data in the food records (ie, unspecified food items being recorded or information on portion size is missing), this information will be added using data from a nationwide study of dietary intake in Sweden [20] or replaced by a standard portion size. This may affect results from the food records. However, such missing information is likely random. To enable long-term follow-up of dietary intake as well as comparison to other studies, participants also respond to an FFQ at baseline and follow-up after 3, 6, and 12 months.

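### The stated 80% power for a 4 mmol/mol HbA1c difference does not follow from the stated inputs: with an SD of 11.8, 84 per group gives about 59%

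*Protocol article*

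**What the plan says.** The section Sample Size and Power Calculations says "A total of 168 patients (84 per group) will provide 80% power at a 5% significance level" and continues "to detect a clinically significant change of 4 mmol/mol" in HbA1c. On variability it says "A standard deviation of 11.8 mmol/mol was estimated based on the average" HbA1c level in Stockholm County in 2016, taken from the national diabetes register. It expects about 20% dropout and sets recruitment at 200, 100 per group.

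Under Study Design, "patients are then randomized 1:1 to the intervention or control group". The Hypothesis section compares the app group with the control group after 12 weeks. The Abstract and the Aim name dietary intake as the primary outcome and list HbA1c among the secondary outcomes.

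The Discussion lists among the trial's strengths "a large sample size, objective assessment of outcomes (eg, measured clinical and anthropometric variables), and a priori calculation of statistical power".

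**The concern.** The paragraph gives a difference, an SD, a group size, a significance level and a power. With two equal groups, any four of these fix the fifth, and here they disagree. The standardised difference is 4/11.8 = 0.34, and 84 per group is too few to detect that with 80% power in a plain two-group comparison.

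What is at stake is how the HbA1c result will be read. A reader who trusts the 80% will take a null result as fair evidence against a 4 mmol/mol effect. On the stated inputs, an unadjusted comparison would miss a true effect of that size about 41% of the time with 84 per group, and about 43% of the time with 80. This is the only sample-size justification in the article, and the Discussion uses it to support the trial's credibility.

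**Working it through.** **Inputs from the article**
- Difference 4 mmol/mol, SD 11.8 mmol/mol, 5% level, 80% power, 84 per group, about 20% dropout, 200 recruited (Sample Size and Power Calculations).
- Two groups, 1:1 (Study Design; Randomization and Blinding).
- Sidedness is not stated. I take two-sided and also show one-sided.

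**Attempt to reproduce 84 per group**

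n per group = 2 × (z₀.₉₇₅ + z₀.₈₀)² × SD² / difference²
= 2 × (1.96 + 0.8416)² × 11.8² / 4² = 136.6

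That is 137 by the normal approximation. The exact t test needs 138. The stated 84 is not reproduced.

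**Power for 4 mmol/mol at SD 11.8, two-sided 5%, noncentral t**

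| Per group | Where it comes from | Power |
|---|---|---|
| 84 | stated | 58.9% (59.4% by normal approximation) |
| 80 | 200 × 0.80 = 160 remaining | 56.8% |
| 100 | no dropout at all | 66.5% |

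**Other readings of the same inputs**
- One-sided 5%: 2 × (1.645 + 0.8416)² × 11.8² / 4² = 107.6, so at least 108 per group. Power at 84 is 70.6%.
- One-sample or paired formula with SD 11.8: (1.96 + 0.8416)² × 11.8² / 4² = 68.3, so 69 (71 by t test). This formula does not describe a two-arm comparison.
- 168 read as the number per group: power 87.2%.

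None of these gives 84 per group at 80% power.

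**What would have to be true for 84 to be right**
- An SD of about 9.2 in place of 11.8; or
- a difference of about 5.1 mmol/mol in place of 4 (5.3 at 80 per group); or
- adjustment for baseline. The variance is then multiplied by 1 − r² for ANCOVA and by 2(1 − r) for a change score, where r is the baseline to follow-up correlation. For 80% power at 84 per group, r must be 0.63 (ANCOVA) or 0.70 (change score). At 80 per group ANCOVA needs 0.65.

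The article gives no value of r, so the values below are assumptions that show the range:

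| Assumed r | ANCOVA, 84 per group | ANCOVA, 80 per group | Change score, 84 per group |
|---|---|---|---|
| 0.5 | 71% | 69% | 59% |
| 0.63 | 80% | 78% | 71% |
| 0.7 | 86% | 85% | 81% |
| 0.8 | 95% | 94% | 93% |

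**The case against.** The strongest reply is that a baseline-adjusted calculation may have been meant. The paragraph speaks of a change, HbA1c is measured at baseline, 3 and 6 months, and the Statistical Analysis section plans generalized estimating equations for time and intervention. If the correlation is 0.7 or more, 84 per group gives at least 80% power for an ANCOVA or a change-score comparison. On that view the figure may be sound and only an assumption went unprinted. It can also be said that HbA1c is secondary, so the figure does not govern the primary test.

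Part of this stands. The 59% power and the roughly 40% chance of a miss belong to an unadjusted comparison at one follow-up. An adjusted analysis could do better, and the true power is not known to be 59%. The secondary status of HbA1c also limits the consequence.

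It does not rescue the paragraph. The 11.8 is derived from the HbA1c level in a register, not from change within patients, and no correlation or SD of change is given. The result depends heavily on that missing value: at a correlation of 0.5 the power is still only 71% with ANCOVA and 59% with a change score. The Statistical Analysis section names t tests as well, and commits to adjusting only for characteristics found to be unbalanced at baseline. Pooling the 3- and 6-month values would add precision, but controls use the app after 3 months, so that is no longer the 12-week contrast in the Hypothesis.

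Nor is this a detail that an article may leave to a fuller document. The article prints the inputs together with a result that they do not produce.

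**Conclusion.** The concern holds. From the article's own difference, SD and group size, a two-sided 5% comparison has about 59% power, not 80%. About 276 evaluable patients would be needed where 168 are stated. With 84 per group, 80% power is reached for a difference of about 5.1 mmol/mol.

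This assumes two equal groups, a two-sided test and no baseline adjustment. One-sided testing raises the power only to 70.6%. Baseline adjustment can bring it to 80% or more, but only with a correlation of at least 0.63 (ANCOVA) or 0.70 (change score), and the article states none. As written, the power claim is wrong or lacks the assumption it rests on. It concerns a secondary outcome, but it is the only power claim made for the trial.

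**What to change.** Correct the Sample Size and Power Calculations paragraph in one of two ways.

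1. **If an unadjusted comparison was meant:** state that with SD 11.8 and a two-sided 5% test, 84 per group gives about 59% power for 4 mmol/mol and 80% power for about 5.1 mmol/mol. Give the values for 80 per group as well (about 57% and 5.3 mmol/mol), since that is what 200 recruited and 20% dropout leave.
2. **If a baseline-adjusted analysis was meant:** say so, commit to adjusting HbA1c for its baseline value whether or not the groups look balanced (ANCOVA is the simplest form), and state the correlation or SD of change relied on, with its source. For ANCOVA the correlation must be at least 0.63 at 84 per group, or 0.65 at 80.

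In either case state the sidedness, and remove or qualify the sample size and power calculation as strengths in the Discussion.

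The cost is wording only. No extra patients are needed. Under the first option the stated power becomes less favourable.

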## Results

The first study participants were recruited in January 2019. Data collection is ongoing. Recruitment is planned to continue until a total of 200 study participants have been included or up to the end of June 2021, whichever comes first. Data collection, including follow-up assessments, will be complete 1 year after recruitment of the last study participant. We expect to publish findings from the study by the end of 2021.

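### Recruiting 200 does not cover the plan's own 20% dropout: 160 patients would remain, against the 168 that the power statement requires

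*Protocol article*

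**What the plan says.** All the figures stand in one paragraph of the protocol article, Methods, Sample Size and Power Calculations:

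- Required number: "A total of 168 patients (84 per group) will provide 80% power at a 5% significance level". The target is a 4 mmol/mol difference in HbA1c, with an SD of 11.8 mmol/mol.
- Expected loss, based on earlier intervention studies: "a dropout rate of around 20% is expected".
- Recruitment target: "To cover for potential dropout, we will recruit a total of 200 patients (100 per group".

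The Abstract repeats the target of 200. The Results section makes it an upper limit, with the earlier of two events ending recruitment: "Recruitment is planned to continue until a total of 200 study participants have been included or up to the end of June 2021". No other section gives a different dropout rate or a different required number.

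**The concern.** The paragraph presents 200 as the number that protects the required 168 against dropout of about 20%. At that rate it does not. A dropout allowance is found by dividing the required number by the expected retention, and 168 divided by 0.80 is more than 200.

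What is at stake is the 80% power claim for HbA1c. A reader of a null HbA1c result would rely on it, and the Discussion lists the a priori power calculation among the trial's strengths. On the plan's own assumptions the claim is not met, even if 84 per group is accepted as correct. Because recruitment ends at 200 or earlier, nothing in the plan makes up the difference.

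**Working it through.** **Inputs**, all from Sample Size and Power Calculations: 168 required (84 per group), dropout 20%, target 200 (100 per group), difference 4 mmol/mol, SD 11.8 mmol/mol, power 80%, significance level 5%. The article does not say whether the test is one- or two-sided; two-sided is assumed here.

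**1. Can the target of 200 be reproduced?**

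- Required number ÷ retention: 168 / (1 − 0.20) = 210, or 105 per group. This is not 200.
- Required number × (1 + dropout): 168 × 1.20 = 201.6, close to 200. Multiplying by 1.2 instead of dividing by 0.8 is a common slip and a plausible origin. The article does not show its step, so this is conjecture, and the point does not depend on it.

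**2. What does 200 leave?**

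- 200 × 0.80 = 160, or 80 per group. Shortfall: 168 − 160 = 8.
- Largest dropout that still leaves 168: 1 − 168/200 = 16%.

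**3. Power if 84 per group is accepted as giving exactly 80%**

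In the normal approximation, the standardised effect at 84 per group is then 1.960 + 0.842 = 2.802, and it scales with the square root of n. At 80 per group:

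- 2.802 × √(80/84) = 2.734
- power = Φ(2.734 − 1.960) = Φ(0.774) = 78.1%

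The noncentral t distribution gives 78.0%. The difference detectable with 80% power becomes 4 × √(84/80) = 4.1 mmol/mol.

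Because the dropout rate is approximate, the same calculation over a range (normal approximation) is:

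| Dropout | Left of 200 | Recruits needed to keep 168 | Power if 84 per group gives 80% |
|---|---|---|---|
| 15% | 170 | 198 | 80.5% |
| 16% | 168 | 200 | 80.0% |
| 18% | 164 | 205 | 79.0% |
| 20% | 160 | 210 | 78.1% |
| 22% | 156 | 216 | 77.0% |
| 25% | 150 | 224 | 75.4% |

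**4. The figure of 84 itself (a separate problem)**

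For a two-sided comparison of two means:

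- n per group = 2 × (1.960 + 0.842)² × 11.8² / 4² = 2 × 7.849 × 139.24 / 16 = 136.6, so 137
- a one-sided 5% test gives 108

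Neither gives 84. With SD 11.8, no baseline adjustment and a two-sided test, the noncentral t gives power of 58.9% at 84 per group and 56.8% at 80. Dropout accounts only for the 2.1 points between these two figures. The fall from 80% to 58.9% comes from the SD.

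For 84 per group to give 80% power, the effective SD would have to be about 9.25. Baseline adjustment with a baseline to follow-up correlation of about 0.62, or a change score with a correlation of about 0.69, would produce that. The article states neither.

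**The case against.** The arithmetic is not disputed. The case on the other side concerns its weight.

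- **Small effect.** Two percentage points of power, or ten recruits, on a dropout rate given only as approximate, change no design decision. This stands, and it limits the point to a correction of the text. It does not rescue the statement, because the approximate 20% would have to mean 16% or less.
- **Secondary outcome.** The power calculation is for HbA1c, while the Abstract and Aim name dietary intake as primary. This stands: the shortfall is in the HbA1c calculation and affects no stated power claim for the primary outcome.
- **160 may be too low for the analysed number.** The article does not tie the 20% to a visit. HbA1c is measured at 3 and 6 months, and the Statistical Analysis section plans generalized estimating equations, intention-to-treat analysis and sensitivity analysis for missing data. A patient lost after month 3 still contributes the 3-month HbA1c, the one measured before controls are given the app. This stands in part: 160 assumes that the full 20% is lost before the HbA1c endpoint. But the sample-size paragraph itself treats dropout as loss from the required 168, and on that logic the allowance is miscalculated.
- **Other problems should not be counted here.** The power figures near 57% to 59% come from the SD, and the June 2021 cutoff is a recruitment rule. Both are fair points. Neither is part of the dropout error, although both mean that there is no slack to absorb it.

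**Conclusion.** The concern holds. On the plan's own figures, 200 recruits leave 160 patients at 20% dropout, 8 fewer than the 168 required. The target consistent with 168 and 20% is 210, and 200 covers at most 16%.

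Taken alone, the cost is about 2 percentage points of power (80% to 78.0%), or a detectable difference of about 4.1 instead of 4.0 mmol/mol. This rests on three assumptions: 84 per group gives exactly 80% power, the test is two-sided at 5%, and the full 20% is lost before the HbA1c measurement. It is a small, definite error in the stated sample size for a secondary outcome and should be corrected.

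**What to change.** Replace the sentence on covering dropout with one of these:

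1. State that 200 recruited with 20% dropout leaves 160 evaluable patients (80 per group), and give the power and detectable difference at that number.
2. State that 200 retains the required 168 only if dropout is 16% or lower.

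The text should not describe 200 as covering 20%. It would help to say which visit the dropout rate refers to.

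Either option costs one sentence and needs no extra recruitment. The first depends on settling the base figure. If a baseline-adjusted analysis justifies 84 per group, the quoted power is about 78%. If the SD of 11.8 stands without adjustment, it is about 57%, which is a much less favourable figure to print. Both parts of the calculation should therefore be corrected together. Raising the target to 210 would not secure 80% power under the stated SD: 137 per group with 20% dropout needs 137/0.80 = 171.25, so 172 per group, or 344 in total.
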